#### Follow-up phase

The study center in Erlangen will contact subjects via letter 6 weeks (t3) and 6 months (t4) after discharge from the inpatient PR program. Provided that participant’s current health status along with any other considerations (e.g., holidays) do not preclude wearing the PA monitor, the device and follow-up questionnaires will be sent to the subjects for t3-PA and t4-PA measurement. If the PA monitor and the questionnaire has not been returned within 2 weeks, postal reminders will be sent.

#### Dropout criteria

This study recruits patients with COPD assigned to PR. In some cases, after the physical examination in the rehabilitation clinic, initial diagnoses are proven incorrect after already having completed the t0 measurement at home. These cases are not classified as dropouts but as being falsely included initially. Dropouts for study phase I are defined as patients who provided an informed consent for phase I but refused to complete the baseline evaluation (t0). Dropouts for study phase II are defined as patients who provided an informed consent for phase II but refused to complete one or more of the following measurements (t1–t4). Additionally, dropouts are classified as patients who withdraw from the study during phase I or phase II and prohibit the use of existing data. Subjects who did not complete treatment, or who did not complete assessment at the end of the inpatient PR but do not explicitly refuse or withdraw from the study, will be followed up. Figure 1 illustrates the flow chart of study subjects.

#### Registration of nonresponders

The registration of all eligible patients and the reporting of the number and sex of eligible patients who do not participate in the study will take place for both study phase I and study phase II.

### Randomization

The randomization of subjects in study phase II is carried out by a study nurse after initial physical examination using an externally provided randomization list from the Friedrich-Alexander-Universität Erlangen-Nürnberg. Randomization is stratified based on the four prognostic dichotomous variables sex (male vs. female), progression of COPD (GOLD stages 1–2 vs. stages 3–4), age (<60 years vs. ≥ 60 years), and type of rehabilitation (PR in patients with stable COPD vs. PR after hospitalization due to subsequent COPD-related airway obstruction). The randomization list is created in blocks with six subjects per block. The study nurse is aware of the allocation in the different strata. The randomization scheme was generated by using the website Randomization.com.

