### Study population

The study will take place within the German rehabilitation system which typically provides an inpatient rehabilitation in a disease-specific rehabilitation clinic for a duration of 3 weeks. Eligible are patients with COPD in all 2011 GOLD classifications A–D [18] and stages 1–4 who are enrolled for PR with the rehabilitation clinic Bad Reichenhall, the largest PR clinic in Germany. Recruitment starts in June 2016 and is likely to be finished in September 2017.

Table 1 provides an overview of all inclusion and exclusion criteria. The study nurse verifies inclusion criteria based on the written information available from the general practitioner who filed the application for PR. At the start of PR the admitting physician confirms the inclusion and exclusion criteria during the initial examination.

**Table 1 Tab1:** Study inclusion and exclusion criteria

Inclusion criteria (*ICD-10*)	Main diagnosis for the pulmonary rehabilitation: physician-confirmed diagnosis of chronic obstructive pulmonary disease (COPD) (International classification code: J44.- at all 2011 GOLD classifications A–D). The diagnosis has to be confirmed in each case by lung function (FEV_1_/VC < 0.7 after bronchospasmolysis) and a respiratory specialist at admission to the pulmonary rehabilitation clinic Age ≥ 18 years
Exclusion criteria	Severe comorbidities, which will affect the results of the outcome parameters much more than pulmonary rehabilitation; for example, cancer or severe cardiac or neurological comorbidities
	Considerable reduction of sight and hearing
	Severe psychiatric condition as a secondary diagnosis
	Lack of ability to speak German

*ICD-10* International Classification of Diseases, version 10

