**Fig. 2 Fig2:**

Standard Protocol Items: Recommendation for Interventional Trials (SPIRIT) figure [37–57]

Six weeks before the start of PR, eligible subjects will be contacted in writing by the PR clinic study nurse. The letter contains detailed information about the process of study phase I. Furthermore, patients are asked for their consent to be contacted via telephone. Persons who agree will be called by the study nurse, provided with further information about the study and asked to participate in study phase I. Participants return written informed consent via a prepaid envelope. This form provides the necessary consent for participation in the t0 measurement. The PA monitor will then be shipped out from the Erlangen study center. Enclosed along with the PA monitor, participants receive precise, illustrated instructions for wearing the PA monitor. Additional telephone support will be available from the Erlangen study center for all questions regarding study phase I, including any accelerometer issues.

Study phase II starts with the beginning of inpatient PR. During initial PR admission assessment subjects of study phase I will be informed about the course of the study phase II (t1–t4). A second signed informed consent is required for participation in phase II of the study. Subjects will then be randomized into two study arms, either the control group (CG) or the intervention group (IG). All subjects will first undergo an initial assessment of PA-related health competence (t1). Before the start of the study interventions (see the “Interventions” section below) in week 2 of the inpatient PR, CG and IG will each receive a short introductory session explaining the use of PA monitors. At the end of the inpatient PR, the assessment battery from t1 will be repeated (t2).

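### The nurse who randomizes knows the allocation within strata and blocks are fixed at six, so allocation is not reliably concealed at entry to phase II

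*Protocol article*

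**What the plan says.** The Randomization section of the protocol article says that assignment is "carried out by a study nurse after initial physical examination using an externally provided randomization list". On the form of the list it says "Randomization is stratified based on the four prognostic dichotomous variables" and "The randomization list is created in blocks with six subjects per block". It gives no other block size. It then adds, of the person doing the assigning: "The study nurse is aware of the allocation in the different strata".

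Two other sections describe who does what before that point:

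- **Study population.** "The study nurse verifies inclusion criteria based on the written information available from the general practitioner" who applied for the rehabilitation. Later, "At the start of PR the admitting physician confirms the inclusion and exclusion criteria during the initial examination".
- **Study flow and recruitment procedures.** Six weeks ahead of rehabilitation, "eligible subjects will be contacted in writing by the PR clinic study nurse", who then telephones those who agree and invites them into phase I. At admission a second written consent is needed for phase II, and randomization follows it. The person who takes this second consent is not named.

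**The concern.** Concealment means that nobody involved in entering a patient can know or infer the next assignment until entry is irrevocable. Here the person who assigns is said to know the allocation, and one fixed block size makes the end of each block predictable.

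The opening is at admission, in three places:

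- the second consent, which can be sought with more or less persuasion;
- exclusions that call for judgment in Table 1, such as severe comorbidity or reduced sight and hearing;
- the order in which patients of the same stratum are entered, with about 12 subjects a week expected at one clinic.

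If more motivated patients tend to enter when the pedometer arm is due, the arms differ before treatment starts. The primary analysis adjusts for baseline physical activity at t0. It does not adjust for motivation or volition, which the protocol itself counts among the determinants of long-term activity. The planned effect is small (d = 0.3), and a larger sample does not shrink a bias of this kind.

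**Working it through.** **Inputs.** Block size six, four two-level stratification factors and a single clinic (Randomization; Study population). 351 complete cases, 30% dropout, and 502 recruited at 251 per group, hence 1:1 (Sample size and power calculation). The predictability figures assume an observer who knows the block size and the earlier assignments in the stratum.

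**Step 1: the plan's own figure.** ANCOVA with f = d/2 = 0.15, two groups, one covariate, 5% two-sided (sidedness is not stated) and 80% power gives N = 351 (power 0.8003). Then 351 / 0.70 = 501.4, rounded up to 502. Both figures reproduce. The sample size does not depend on how assignments are released.

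**Step 2: assignments certain in advance.** A 1:1 block of six has C(6,3) = 20 equally likely sequences. An assignment is certain once one arm has used its three places.

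- 6th: always, probability 1.
- 5th: the last two places belong to the same arm, 2 × C(4,1) / 20 = 8/20 = 0.40.
- 4th: the first three places belong to the same arm, 2/20 = 0.10.
- 1st to 3rd: 0.

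Expected number certain: 1 + 0.40 + 0.10 = 1.5 of 6, or 25%.

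**Step 3: assignments guessed correctly.** The best strategy guesses the arm used less so far in the block. With m = 3, the expected number correct is m + 2^(2m−1) / C(2m, m) − 1/2 = 3 + 32/20 − 0.5 = 4.1 of 6, or 68.3%. Under concealment it is 50%.

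**Step 4: scale.** If all 502 were randomized in complete blocks, 502 × 0.25 ≈ 125 assignments would be certain and 502 × 0.683 ≈ 343 guessed correctly, against 251 by chance. These are upper guides for two reasons. The 502 are counted from t0, before randomization. And 2^4 = 16 strata hold on average 502 / 16 = 31.4 patients, or 31.4 / 6 = 5.2 blocks, so some blocks stop before their late, predictable places.

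**Step 5: the other reading.** If the nurse can see upcoming entries, 100% are knowable and block size is irrelevant.

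**Step 6: would a larger fixed block be enough?** The same enumeration for a block of eight gives 1.6 of 8 (20%) certain and 66.6% guessable. Changing the block size alone helps little.

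**The case against.** The strongest reply is that the text supports less than a quick reading suggests. Four parts of it deserve weight.

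- **An open list.** A reader might infer that the nurse works from a list with all future entries in view. The article does not say so; the awareness sentence may refer only to assignments already made. That sealed envelopes or telephone release go unmentioned is no evidence either, since a condensed article may leave this to the full protocol. This stands, so 100% is one reading and not a finding. The milder reading still leaves up to 25% certain.
- **One person controlling everything.** A reader might infer that one nurse screens, recruits, obtains consent and randomizes. The documented letter, call and referral check belong to phase I, weeks before assignment. At admission the physician confirms eligibility. That the nurse mentioned in three sections is one person is natural but not stated. This narrows the opening without closing it.
- **Existing safeguards.** The list is produced outside the clinic, only phase I participants can enter, the sample is described as consecutive, and eligible nonparticipants are counted in both phases. External production protects how the sequence is generated, not its concealment. Nonparticipants are reported by number and sex only, so selection on motivation would not show. Patient masking and an analyst outside the study act after assignment.
- **Practical difficulty.** Exploiting the blocks means tracking past assignments across 16 strata, and most assignments are still not certain. This is fair, but the nurse is said to have exactly that knowledge by stratum.

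No motive for the nurse to steer patients is documented. That bears on how likely selection is, not on whether it was possible.

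**Conclusion.** The point holds. It rests on a positive statement that the person who randomizes knows the allocation, together with one fixed block size at one clinic, and not on missing detail. Allocation is not reliably concealed at phase II consent and entry. On the milder reading, up to 25% of assignments are certain in advance and about 68% guessable, given knowledge of block size and past assignments and complete blocks. If upcoming entries are visible, all are knowable.

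Two further inferences are tempting and not supported. A reader might put a figure on the resulting bias in physical activity; the document gives nothing from which to derive its size or direction. A reader might also conclude, because t1 is described after randomization, that the trial lacks a pre-allocation baseline. The primary comparison uses t0, measured two weeks before rehabilitation, so it is not affected.

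**What to change.** **For patients still to be randomized.** Hold the list at the Erlangen study center. Release each assignment only after phase II consent is signed and eligibility confirmed, and record the time of each step. Use randomly varied block sizes that are not disclosed to the clinic. Central release is the essential part; varied blocks support it. The cost is a new list and a release step at an existing center, plus a short delay before allocation. The delay is harmless because the study sessions start only at the end of the second week. The sample size stays at 351 and 502. Recruitment was expected to end in September 2017 and the article appeared on 29 August 2017, so this part may reach few patients.

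**For patients already randomized.**

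- State whether upcoming assignments were visible to the nurse, and who took the phase II consent.
- Compare t0 physical activity and other pre-allocation characteristics by arm and by how predictable the assignment was (block position within stratum). Characteristics other than the four stratification factors are the informative ones.
- Report the lack of reliable concealment as a limitation.

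This costs only analysis and reporting time. A reassuring comparison should not be oversold. With at most about 125 certain assignments, or some 63 per arm, the difference detectable with 80% power at two-sided 5% is about (1.96 + 0.84) × √(2/63) = 0.50 SD, larger than the planned effect of 0.3.

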### Sample size and power calculation

A consecutive sample of 351 PR patients is needed. Pedometer-based interventions are among the most effective intervention components to promote PA in everyday life [8]. Meta-analysis has shown, in comparison to control groups, an average mean effect size of 0.68 on PA which represents an increase of 2000 steps per day [12]. The long-term effect on PA of standard inpatient PR in people with COPD is assumed to be small [16]. In comparison to standard PR we expect a small effect (*d* = 0.3) at t4. The power calculation (by means of software G*Power 3.0) with respect to the primary target (analysis of covariance to t4, mean effect size of *d* = 0.3, an alpha error level of 5%, and statistical power of 80%) results in a required sample of at least 351 subjects with complete data. In a preliminary pilot study, a generally high willingness to participate of 96% was recorded. A dropout of 30% from baseline measurement t0 to t4 is estimated based on the pilot study. With this dropout rate, the recruitment of a total of 502 subjects (251 subjects per group) is necessary. The study sample size is adequate for the determination of PA predictors after rehabilitation and with a weekly average of 12 subjects and a conservative recruitment rate of 66%, the study aims should be reached within the recruiting period of 15 months.

### Interventions

#### Control arm

The control group (CG) will receive standard PR. Standard PR is an intensive and comprehensive inpatient PR in a specialized German rehabilitation clinic. This PR is described in further detail below. In addition, the CG receives a “behavior placebo” intervention during their PR. This intervention contains playful PA and revisions of information on PA (knowledge on exercise recommendations, knowledge on possibilities of self-regulation of endurance training exercise intensity) obtained earlier during patient education of the standard PR. Similar to the IG subjects, the CG receive a booklet that looks identical to the PA diary used in the IG. This booklet contains a repetition of PA-related information from the standard PR curriculum.

PR in the Bad Reichenhall Clinic. In Germany, PR is usually carried out as inpatient rehabilitation and generally lasts 3 weeks, an extension of 1 to 2 weeks is possible if necessary. PR is a comprehensive, multidisciplinary intervention based on an initial assessment followed by a combination of patient-tailored therapies [1, 19]. In the Bad Reichenhall Clinic PR lasts an average of 25 days, is tailored to the patients’ individual needs and includes the following obligatory main components: checking and, if required, adjusting the current COPD medication according to COPD guidelines; physical exercise (4–5 units/week of endurance exercise (45 min) and 3 units/week of strength exercise (45 min) per week, and 7 units/week whole-body vibration muscle training); structured COPD patient education (6 h of patient education COPD + 1 h inhaler device training), respiratory physiotherapy in groups (pursed lips breathing and other breathing and coughing techniques (2 units/week of 45 min)). Optional components include a comprehensive smoking-cessation program (at least 8 units), mucolytic physiotherapy, inspiratory muscle training (IMT), neuromuscular electrostimulation (NMES), saline inhalation therapy, psychological interventions and social counseling (individual and groups), nutritional counseling, patient education concerning long-term oxygen therapy, and occupational therapy including counseling on assistive devices. PR in Bad Reichenhall Clinic is implemented by an interdisciplinary rehabilitation team including experienced pneumologists who bear overall responsibility and coordinate the program along with further health professionals including physiotherapists, exercise therapists, occupational therapists, psychologists, social workers, nurses and nutritionists.

For all patients – IC and CG – receiving PR in the Bad Reichenhall Clinic, treatment includes several intervention components addressing the promotion of PA. Additional file 1 lists the behavior-change techniques (BCT) included in standard care in the Bad Reichenhall Clinic according to the taxonomy of BCT from Michie et al. [11].

#### Intervention arm

Subjects in the intervention arm will receive the same standard inpatient PR program as the control arm. Instead of the placebo intervention of the CG the IG will additionally receive a pedometer-based PA BCI.

The central components of the BCI include the following behavior-change techniques (BCT):Instruction on how, where and when to perform the behaviorPrompt goal setting for PAPrompt self-monitoring of behaviorFeedback on behavior

The BCI integrates the most frequently applied BCT for PA promotion in patients with COPD [20]. Additional file 2 explicates the sequence of the two BCI lessons and defines the used BCT with regard to the BCT taxonomy [11].

The BCI will consist of two 45-min sessions. The first lesson is placed in the end of the second week of PR and the second lesson will take place in the middle of the third week of PR. During lesson 1 of the BCI, subjects receive a pedometer and booklet containing a PA diary and PA-related information (recommendations for exercise and PA for patients with COPD). Subjects keep the pedometer and the booklet after their PR discharge. The intervention replaces standard exercise therapy and for this reason the total amount of therapy is identical. The BCI is delivered in open groups (varying composition of subjects possible) with six to 12 patients. An exercise therapist from the clinic will hold both lessons. As BCT included in the sessions relate to PA, the lessons take place in a gymnasium.

With regard to session length, placement (2 × 45 min in weeks 2 and 3 of the PR) and group composition, the CG lessons are identical to the IG.

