### Data analysis

#### Statistical analysis and evaluation

Regarding the primary objective, a baseline-controlled comparison (covariance) of the post values between the initial assigned control and the intervention treatment group (intention-to-treat analysis) at the time points t3 and t4 will be provided for statistical analysis.

For the secondary objective a cluster-based analysis method will be used for longitudinal records (e.g., linking of clusters after removal of a residue (LICUR); [25]). In this case the analysis creates separate clusters for each measurement using the comprehensive assessment battery for t1 and t2 and especially using the accelerometer PA data for t0, t3 and t4. The second step of the cluster-based analysis links separately created clusters in a longitudinal way.

A strategy for dealing with missing data will be developed in cooperation with a biostatistician. If adequate and realistic, missing data will be substituted by multiple imputation.

The processing of PA monitoring data as the primary outcome will be conducted as follows: the PA monitor will be worn for seven consecutive days with a minimum of four valid days inclusive of a weekend day [26–28]. A day is considered valid if subjects wear the device for ten or more waking hours [26–28], where non-wear time is set at 60 min of zero counts of which up to 2 min may be within the 0–100 count range [28, 29]. Current research points towards avoiding the use of direct monitor outputs such as energy expenditure estimations due to issues with reliability [21, 30]. Consensus points towards the use of both sedentary and moderate to vigorous physical activity (MVPA) cutoff points where sedentary activity is seen as 0 to > 100 counts per min [27, 29, 31, 32] and MVPA as > 1952 counts per min [29]. While the use of the LFE filter to calculate steps is not recommended, it may be applicable during data analysis of cutoff points for older adults [33, 34]. Future work on defining cutoff points in clinical populations will be considered.

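### Lessons in both arms are given in groups, but the sample size and the stated ANCOVA make no allowance for correlation within session groups; the likely effect is small and depends on an unstated ICC

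*Protocol article*

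**What the plan says.** All references are to the protocol article.

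- **Randomization:** individual patients are allocated from a stratified list in blocks of six.
- **Intervention arm:** two 45-minute lessons, late in week 2 and in the middle of week 3 of rehabilitation. On delivery: "The BCI is delivered in open groups (varying composition of subjects possible) with six to 12 patients". On the control lessons, the section says that with regard to length, placement and "group composition, the CG lessons are identical to the IG". Lesson content differs by arm, so a session group contains study patients of one arm only.
- **Sample size and power calculation:** "In comparison to standard PR we expect a small effect (*d* = 0.3) at t4", with "an alpha error level of 5%, and statistical power of 80" per cent, which "results in a required sample of at least 351 subjects with complete data". Then "A dropout of 30% from baseline measurement t0 to t4 is estimated based on the pilot study", so that "the recruitment of a total of 502 subjects (251 subjects per group) is necessary". No group size, ICC or design effect enters.
- **Statistical analysis and evaluation:** the primary analysis is "a baseline-controlled comparison (covariance) of the post values" between the arms as assigned, at t3 and t4. No session or therapist term is named. The cluster-based method in the same section sorts patient profiles for the secondary objective and does not deal with delivery groups.

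**The concern.** This is an individually randomised group-treatment design in both arms. Patients taught together share how that session went and the dynamics of that group. Because each session group sits within one arm, such shared effects do not cancel from the treatment contrast; they add to its variance.

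An analysis of covariance that treats patients as independent leaves that variance out. With a positive within-group correlation, its confidence intervals are too narrow, its primary p-value is anti-conservative, and the planned number of patients carries less information than the power statement assumes. The Discussion describes the sample size as adequately powered, and that description rests on independence.

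**Working it through.** **1. Reproduce the plan's figure.** Inputs from the sample size section: d = 0.3, hence f = d/2 = 0.15; alpha 5% (two-sided, which reproduces the figure; sidedness is not stated); two groups, one covariate. F test with noncentrality N × f², 1 and N − 3 degrees of freedom:

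- N = 350: power 0.7991
- N = 351: power 0.8003

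So 351 is the smallest N that reaches 80% with independent patients. Dropout: 351/0.70 = 501.4, rounded up to 502. Both figures are arithmetically right and contain no clustering allowance.

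**2. Study patients per session.** The sample size section gives a weekly average of 12 subjects and a recruitment rate of 66%: 12 × 0.66 = 7.9 per week. This reading fits the stated recruiting period: 502/7.92 = 63.4 weeks, against 15 × 52/12 = 65 weeks. Per arm that is 7.92/2 = about 4 per week. Each patient's lesson 1 falls at a fixed point of the stay, so weekly sessions are a reasonable assumption, though the frequency is not stated. With 30% dropout, 3.96 × 0.70 = about 2.8 are analysed. That dropout counts from t0, so part of it falls before randomisation; about 3 to 4 analysed patients per session is a fair range. The lower limit of the stated group size, 6, is shown as a less favourable case.

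**3. Effect of an assumed ICC.** The article gives none; 0.01 to 0.05 is an assumption. With m analysed patients per session:

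- design effect DE = 1 + (m − 1) × ICC
- effective N = 351/DE, with power from the F test in step 1
- type I error of the unadjusted test = 2 × [1 − Φ(1.96/√DE)]
- correct interval width relative to the unadjusted one = √DE

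Example, m = 4 and ICC 0.05: DE = 1 + 3 × 0.05 = 1.15; effective N = 351/1.15 = 305; power 74%; 1.96/√1.15 = 1.83, giving type I error 6.8%; √1.15 = 1.07.

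| m | ICC | DE | Effective N | Power | Type I error | Interval width |
|---|---|---|---|---|---|---|
| any | 0 | 1.00 | 351 | 80% | 5.0% | × 1.00 |
| 2.8 | 0.01 | 1.02 | 345 | 79% | 5.2% | × 1.01 |
| 2.8 | 0.05 | 1.09 | 322 | 77% | 6.0% | × 1.04 |
| 4 | 0.01 | 1.03 | 341 | 79% | 5.3% | × 1.01 |
| 4 | 0.05 | 1.15 | 305 | 74% | 6.8% | × 1.07 |
| 6 | 0.01 | 1.05 | 334 | 78% | 5.6% | × 1.02 |
| 6 | 0.05 | 1.25 | 281 | 71% | 8.0% | × 1.12 |

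Open groups are not fixed clusters, so this design effect is an approximation.

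**The case against.** **The analysis may be specified elsewhere.** The article gives the primary analysis in one sentence, and the error structure could be set in a statistical analysis plan that is not shown. This stands: the analysis half of the point concerns only what the article states. It does not reach the power half, because 351 and 502 are fixed here.

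**The ICC may be close to zero.** Exposure is two short lessons within a stay averaging 25 days, group membership varies, and the outcome is measured 6 weeks and 6 months after discharge. This also stands, and is why the size can only be given as conditional.

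**Baseline adjustment may restore the power.** If d = 0.3 is on the unadjusted scale (not stated), a baseline–outcome correlation r reduces the variance by 1 − r². A value of about 0.29 offsets DE 1.09 (1 − 1/1.09 = 0.083, square root 0.29), and about 0.45 offsets DE 1.25 (1 − 1/1.25 = 0.20, square root 0.45). So it cannot be said outright that power is below 80%. The gain would not, however, correct a standard error that ignores the groups.

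**Stronger readings that the article does not support:**

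- *Power of 67% and type I error of 9.4%.* These follow from 12 per group with 70% retained (m = 8.4) and ICC 0.05 (DE 1.37). They pair the largest permitted group with the top of an assumed range, whereas planned accrual points to about 4 study patients per arm per week.
- *Season as a shared cause.* The arms recruit concurrently and their lessons have the same placement, so calendar time is largely crossed with arm and mostly cancels.
- *Therapist clustering in both arms.* An exercise therapist is named for the intervention lessons only. Who leads the control lessons is not stated, nor whether therapists are specific to one arm.

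**Conclusion.** The point holds in a limited form. The group delivery in both arms and the exact reproduction of 351 under independence are established from the article. It follows that the stated power contains no allowance for correlation within session groups, and that the analysis as described has none either.

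How much this matters is not established. For an assumed ICC of 0.01 to 0.05 and 3 to 4 analysed patients per session, it costs about 1 to 6 points of power and adds 0.2 to 1.8 points to the type I error. At 6 per group the cost reaches 9 and 3.0 points. At an ICC of zero there is no cost. These figures rest on the assumed ICC, weekly sessions and an approximate design effect.

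A reader might infer that the sample size is miscalculated or that the trial must recruit more. Neither follows: 351 and 502 are correct for the stated inputs, and the documents give no ICC from which a larger target could be justified. The change is worth making because it is cheap and because session membership, if never recorded, cannot be modelled later.

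**What to change.** 1. Record for each patient, in both arms, the session attended for each lesson, with its date and therapist. The article does not say whether attendance is already logged; for patients treated before the change, it should be stated whether this can be reconstructed.
2. In the primary comparison, keep the baseline-adjusted model and add a random intercept for the lesson-1 group, with Satterthwaite or Kenward–Roger degrees of freedom, since the groups are small.
3. Because groups are open and lesson 2 may bring a different composition, add cluster-robust standard errors or a multiple-membership model as a sensitivity analysis.
4. Report the estimated ICC with the primary result.
5. Restate the power as conditional on an assumed ICC and session size, for example with a short table like the one above. Keep the recruitment target.

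Cost: the session details to be recorded for each patient, a line in the analysis plan, slightly wider intervals and a slightly less favourable stated power. If the ICC proves negligible, the results will hardly change and the report can show that.
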